### Measurements

Changes in renal function will be documented by annually measuring creatinine clearance from a 24-hour urine sample and measurement of the serum creatinine. Quality of life will be assessed through questionnaires that will be filled out by all participants annually. Markers of vascular damage will be recorded annually in a proportion of the patients. These markers address different aspects like endothelial function, arterial compliance and atherosclerosis in various vascular beds. Pulse wave analysis (PWA) and pulse wave velocity (PWV) will be measured in approximately 300 patients. Aortic pulse wave forms and aortic pulse wave velocity are indicators of arterial stiffness. PWV has been shown to be an independent predictor for cardiovascular risk[23,24]. PWA and PWV measurements have been validated and can be measured in a reproducible manner[25]. Carotid intima media thickness (CIMT) evaluation through B-mode sonography will also be measured in approximately 150 patients. Increased CIMT is associated with an elevated risk of cardiovascular disease[24]. Change in CIMT has been shown to result from risk factor modifications in a variety of populations[26]. CIMT measurement has been validated and shown to be reproducible[27].

Blood pressure will be recorded twice per year using a non-invasive automated oscillometric device. Patients will stay in a supine position for 30 minutes, blood pressure will be recorded every three minutes. The last five measurements will be used for analysis. Conventional office readings using the auscullatory method will also be documented.

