### Baseline evaluation and randomization

Table 1 summarizes the data collected at baseline evaluation. After the baseline evaluation, the patient will be randomized to either nurse practitioner care or physician care. Randomization to treatment is stratified by center and renal transplant status using a web-based randomization module and performed in predefined blocks of certain numbers of patients.

**Table 1 T1:** Data collection

Visit	Baseline 1	Visit 2	Visit 3	Visit 4	Visit 5
Month	0	3	6	9	12

Informed Consent	x				
Demographic data	x				
Medical history	x				
In- and exclusion criteria	x				
Randomization	x				
Endpoints		x	x	x	x
Weight	x	x	x	x	x
Waist-hip ratio	x				x
Ankle-Brachial Index	x				x
RR and HR in sitting position	x	x	x	x	x
RR 30 minutes Dynamap	x		x		x
Smoking habit	x	x	x	x	x
Medication use	x	x	x	x	x
Three monthly Laboratory evaluation^a^	x	x	x	x	x
Annual Laboratory evaluation ^b^	x				x
ECG	x				x
PWV (Proportion of patients)	x				x
Carotid-IMT (Proportion of patients)	x				x
Questionnaires ^c^	x				x

a: Three monthly Laboratory evaluation: Hematology: Hb, Ht, trombocyte count; Chemistry: sodium, potassium, calcium, phosphate, bicarbonate, urea, creatinine, albumin; Urinalysis: spot urine creatinine, albumin, total protein

b: Annual Laboratory evaluation: Hba1c, uric acid, PTH, total-cholesterol, HDL-cholesterol, LDL-cholesterol, triglycerides; Urinalysis: 24 hr urine sodium, creatinine, albumin, total protein

c: Questionnaires: Quality of Life: SF-36, EQ-5D; Physical activity: SQUASH; Dietary composition; Erectile dysfunction

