### Statistical methods

Group sequential (or interim) analyses will be performed using the double triangular test as described by Whitehead [42] and implemented in the computer program PEST version 4 [43]. The analyses will be performed by an independent data safety monitoring board (DSMB) consisting of a nephrologist, an internist and a statistician. They meet every 6 months to monitor various aspects of the study, including recruitment, adverse events and interim analyses of the primary endpoints.

The results of the study will be analyzed following the 'intention to treat' principle. This means that subjects will be analyzed according to the group they have been allocated to by the randomization. Results will be presented as Kaplan-Meier curves for the two treatments and the difference between the treatments will be analyzed using a log-rank test. For the primary outcome variables the log-rank test will be adjusted for the effect of the cumulative data analyses. Results will be presented for all cause mortality and CV events separately.

The primary analysis of CIMT progression wiw ll be performed using a linear random coefficient (Laird-Ware) model using real visit days, treatment and clinical center as independent variables. For each participant, the intercept and slope of CIMT change over time is assumed to be a normally distributed random variable with different means for the two treatment groups. The mean slope for the nurse practitioner group will be compared to that for nephrologist-care group using linear contrasts and a 5% significance level. Additional exploratory analyses will evaluate the impact of including baseline IMT, lumen diameter, ultrasound reader, and center as additional co-variates.

The data analytic approach to arrive at the PWV outcome variable is similar to that of the CIMT outcome. Adjustments that will be taken into account in the estimates are changes in MAP and changes in heart rate, since both are closely related to PWV.

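### The primary CIMT slope model gives each arm its own baseline mean although baseline CIMT is measured before randomisation; the test is valid but gives up some precision

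*Protocol article*

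**What the plan says.** The Statistical methods section of the protocol article says the primary analysis of CIMT progression is "performed using a linear random coefficient (Laird-Ware) model using real visit days, treatment and clinical center as independent variables". It lets both the starting level and the rate of change vary between participants, and each of these two quantities "is assumed to be a normally distributed random variable with different means for the two treatment groups". The test compares mean slopes: the nurse practitioner mean "will be compared to that for nephrologist-care group using linear contrasts and a 5% significance level".

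The same paragraph then plans secondary looks: "Additional exploratory analyses will evaluate the impact of including baseline IMT, lumen diameter, ultrasound reader, and center as additional co-variates". For pulse wave velocity it says only this: "The data analytic approach to arrive at the PWV outcome variable is similar to that of the CIMT outcome", with adjustment for changes in mean arterial pressure and heart rate.

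On timing, the section on baseline evaluation and randomisation states: "After the baseline evaluation, the patient will be randomized". Table 1 lists carotid IMT and PWV at month 0 and month 12, and the Measurements section makes them annual. On size, the Measurements section says: "Carotid intima media thickness (CIMT) evaluation through B-mode sonography will also be measured in approximately 150 patients"; PWV is planned in about 300.

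**The concern.** A baseline value taken before allocation has the same expected value in both arms, and any observed difference is chance. A model with a separate mean intercept per arm estimates a difference that is known to be zero. The estimated intercept and slope differences are usually correlated, so fixing the first at its known value sharpens the second. Leaving it free throws that away. At stake is the width of the confidence interval for the CIMT slope difference, and hence power, in a small subset studied for a secondary outcome.

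Two smaller points sit in the same paragraph. First, baseline IMT is offered as a covariate in a model whose natural first response is that same measurement; if the month-0 value stays in the response, covariate and response coincide at time zero and the random-intercept and residual structure is misspecified. Second, centre is listed as an additional covariate although it is already in the primary model.

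**Working it through.** **Plan's own figure.** There is none to reproduce. The Power analysis section sizes the trial for the clinical composite only; no SD, effect or power is given for CIMT or PWV.

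**Inputs from the document.** About 150 patients, taken as 75 per arm; visits at years 0, 1, 2, 3, 4, 5; five years of follow-up.

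**Inputs assumed.** Intercept SD s0 = 0.20 mm; slope SD s1 = 0.01-0.03 mm/year; error SD se = 0.05-0.10 mm; intercept-slope correlation r = -0.3 to 0.3; complete data; known covariance; centre ignored.

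**Formula.** With complete balanced data, the per-patient covariance matrix of the least-squares intercept and slope has entries

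- A (intercept variance) = s0² + se² × 55/105
- B (covariance) = r·s0·s1 - se² × 15/105
- C (slope variance) = s1² + se² × 6/105

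because the six times sum to 15, their squares sum to 55, and 6 × 55 - 15² = 105. With free intercepts the variance of the slope difference is 2C/75. With a common intercept it is (2/75)(C - B²/A). The ratio is 1 - B²/(AC), which cannot exceed 1.

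**Worked case.** s0 = 0.20, s1 = 0.02, se = 0.10:

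- A = 0.04 + 0.01 × 0.5238 = 0.04524; C = 0.0004 + 0.01 × 0.05714 = 0.000971
- r = 0: B = -0.001429; B²/(AC) = 0.046; ratio 0.954
- r = -0.3: B = -0.0012 - 0.001429 = -0.002629; B²/(AC) = 0.157; ratio 0.843
- r = 0.3: B = 0.0012 - 0.001429 = -0.000229; B²/(AC) = 0.001; ratio 0.999

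The free-intercept standard error is √(2 × 0.000971/75) = 0.0051 mm/year.

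**Whole grid** (variance ratio, common over free intercept):

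| s1 | se | r = -0.3 | r = 0 | r = 0.3 |
|---|---|---|---|---|
| 0.01 | 0.05 | 0.909 | 0.987 | 0.994 |
| 0.01 | 0.10 | 0.865 | 0.933 | 0.977 |
| 0.02 | 0.05 | 0.892 | 0.994 | 0.968 |
| 0.02 | 0.10 | 0.843 | 0.954 | 0.999 |
| 0.03 | 0.05 | 0.892 | 0.997 | 0.952 |
| 0.03 | 0.10 | 0.843 | 0.969 | 0.998 |

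The variance cut is 0-16% overall and 0.3-6.7% at r = 0. In standard-error terms the largest cut is 1 - √0.843 = 8%, and 1 - √0.933 = 3.4% at r = 0. An effect with 80% power under free intercepts would have at most Φ(2.80/√0.843 - 1.96) = 86%. With visits at years 0-2 only and r = 0, the cut is 2-10%. Widening the assumptions to s0 = 0.15-0.20 and r = -0.5 to 0.5 (years 0-5) gives ratios of 0.67-1.00.

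**Baseline as covariate and response.** A simulation of 120 trials (s0 = 0.20, s1 = 0.02, se = 0.08, r = -0.3) gave these median model standard errors for the slope difference: 0.00451 with free intercepts, 0.00422 with a common intercept, 0.00475 with baseline IMT used twice as a main effect, and 0.00448 with it used twice and interacting with time. No bias in the slope was visible. The empirical SDs of the estimates were 0.00412-0.00422 for all four models; with 120 trials their Monte Carlo error is about 1/√(2 × 119) = 6%, too coarse to confirm a gain of this size. What the run shows is that double use does not recover the precision in the reported standard error, and as a main effect lengthens it.

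**The case against.** The strongest reply is that nothing here is an error. A random-coefficient model with arm-specific intercepts and slopes is standard, and its slope contrast is unbiased with a valid test. That stands in full. It also stands that the gain rests on variances the documents do not give, that it reaches 9-16% only at the assumed correlation of -0.3, and that it can be practically nil.

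A second reply is that equal baseline means imply equal model intercepts only if trajectories are linear from month 0. An early effect is conceivable, given blood pressure targets and the plan's own remark that PWV depends on mean arterial pressure. If the effect were a unit step after month 0, the free-intercept slope would be 2.5/17.5 = 0.143 per year. The common-intercept slope would be 0.143 - 0.476 × B/A, which runs from 0.126 to 0.177 over the grid. Both models turn the step into a slope, and a step already breaks the linear model the plan states, so this does not rescue free intercepts as the primary choice. It is a good reason to keep them as a sensitivity analysis.

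A third reply is that double use of baseline IMT is inferred. The article does not say whether the month-0 value stays in the response for the exploratory model, and the full protocol may settle it. That stands, and the point is therefore conditional. These analyses are exploratory and cannot affect the primary CIMT test.

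**Conclusion.** The point holds as a small, nearly free improvement to a secondary analysis. The plan frees the mean intercepts that its design makes equal under its own linear model. The cost, under the stated assumptions, is 0-16% of the variance of the CIMT slope difference (about 0-7% at zero correlation). It may be negligible.

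A reader might infer more, and the documents do not support it:

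- That the CIMT comparison is biased, or exposed to regression to the mean. Chance baseline imbalance averages out over randomisations and its variation is already in the standard error.
- That baseline adjustment spoils the primary analysis. It appears only among exploratory analyses; any loss in the primary test comes from the free intercepts alone.
- That the PWV analysis has the same feature. The text says only that the approach is similar, and no PWV variances were examined.

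The clinical composite endpoint is untouched.

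**What to change.** Specify the primary CIMT model with one baseline mean common to both arms plus time, treatment-by-time and centre, with random intercept and slope, and test treatment-by-time. Keep the model with arm-specific intercepts as a sensitivity analysis against an early, non-linear effect. Apply the same to PWV if it uses the same intercept-and-slope model, and say so.

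In the exploratory analysis, either drop baseline IMT as a covariate or remove the month-0 value from the response when it is used. Delete centre from the list of additional covariates.

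The cost is a few lines of analysis-plan wording: one fewer parameter in the primary model and one extra model run as sensitivity. No data collection or sample size changes.

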## Discussion

### Limitations of the study

There are several limitations to the study mostly due to unavoidable decisions.

1. Although many patients receiving standard care are not treated according to current guidelines it is ethically not possible to withhold information and advice on these guidelines from the control group. Therefore all patients receive information about risk factor management and all physicians are informed about the treatment goals. This may result in improved treatment in the control group thereby attenuating the potential difference in cardiovascular events between the two treatment arms.

2. Due to the sort of intervention blinding is not possible for patients or physicians. This is unavoidable since some physicians will be treating or supervising both physician care and nurse practitioner care patients. Again, attenuation of group differences may occur.

3. The multifactorial intervention will make it impossible to single out one aspect of the intervention as being the most beneficial. Since trials establishing the exact amount of risk reduction per risk factor intervention are missing in patients with mild to moderate renal dysfunction, such information would have been most useful. As pointed out earlier however the choice for a multifactorial design has received ample consideration. As a consequence of this choice for a multifactorial approach sample size is too small to allow for a definite statement about a single risk factor. A study large enough to establish the benefits of one aspect of the intervention would require thousands of patients and the logistics and funding necessary to realize this are not present for investigator driven research.

## Conclusion

Cardiovascular risk in patients with CKD is very high, multifactorial in origin and present early in the course of CKD. Effectively addressing risk factors will reduce cardiovascular risk significantly. A multifactorial approach with the aid of nurse practitioners has been shown to be effective in other high-risk populations. The MASTERPLAN trial is designed to establish the effects of such a multifactorial approach in patients with mild to moderate renal insufficiency. The MASTERPLAN trial is a unique multicenter randomized clinical trial because it investigates the effects of a multifactorial approach to reduce cardiovascular events in a population until now rarely targeted despite a huge cardiovascular risk. The employment of the nurse practitioner provides a valuable means of implementing the multifactorial intervention.

## Appendix A

The Cockcroft-Gault equation

The Cockcroft-Gault equation modified to correct for body surface area (effective from april 15^th ^2005).

Body Surface Area will be estimated using the formule by Dubois and Dubois.

